## 4. Discussion

This study aims to address the critical challenge of antiplatelet resistance in patients undergoing coronary artery bypass grafting (CABG). Despite the widespread use of dual antiplatelet therapy, a significant proportion of patients exhibit laboratory-confirmed resistance to aspirin and/or clopidogrel. This resistance, whether transient due to perioperative platelet turnover or persistent due to genetic, metabolic, or inflammatory mechanisms, has been associated with adverse cardiovascular outcomes such as graft occlusion, myocardial infarction, and increased mortality risk [5,6].

Current guidelines do not recommend routine PFT for CABG patients, primarily due to a lack of high-quality prospective data correlating platelet reactivity profiles with postoperative outcomes [9,10]. As a result, postoperative antiplatelet management remains largely empirical, contributing to variability in prescribing practices and uncertainty regarding the role of PFT [8]. The present study seeks to address this gap by prospectively evaluating perioperative platelet reactivity and correlating these findings with clinical outcomes to determine whether PFT can serve as a reliable risk stratification tool for CABG patients.

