## Abstract

Background: Coronary artery bypass grafting (CABG) is a well-established revascularization strategy for patients with multivessel coronary artery disease. The effectiveness of CABG is significantly influenced by antiplatelet therapy aimed at maintaining graft patency and reducing thrombotic complications. However, substantial inter-individual variability exists in platelet function responses to standard therapies such as aspirin and clopidogrel, leading to antiplatelet resistance. This variability has been linked to increased risks of myocardial infarction, stroke, and early graft failure. Platelet function testing (PFT) offers a potential strategy to identify resistance and guide more personalized antiplatelet therapy. This study aims to evaluate the association between perioperative platelet function test results and clinical outcomes following CABG. By assessing platelet responsiveness at multiple timepoints and correlating findings with postoperative events, the study seeks to determine whether PFT can stratify risk and improve patient management. Methods: This is a prospective, single-centre, observational cohort study conducted at a tertiary NHS cardiac surgery centre. Patients having elective or urgent isolated CABG will be enrolled and undergo perioperative PFT using the TEG6s system. Clinical outcomes will be monitored for 12 months postoperatively, with primary endpoints assessing the correlation between platelet function results and major adverse cardiovascular and cerebrovascular events (MACCE). Secondary endpoints will include the prevalence of antiplatelet resistance, demographic predictors, and the feasibility of integrating PFT into clinical workflows. Results: This study will report the prevalence of aspirin and clopidogrel resistance in CABG patients based on TEG6s PFT, as well as the correlation between platelet function results and MACCE, postoperative bleeding, and the need for surgical re-exploration. Additionally, it will examine the associations between demographic and clinical factors—such as diabetes status, renal function, BMI, and surgical technique—and variability in platelet responsiveness. The feasibility of incorporating PFT into perioperative workflows will also be evaluated, assessing whether results could support personalized antiplatelet management in future clinical trials. Conclusions: Findings from this study will provide real-world evidence regarding platelet function variability in CABG patients and suggest that PFT may identify those at increased risk of thrombotic complications. This exploratory analysis supports the need for larger interventional trials aimed at optimizing individualized postoperative antiplatelet therapy to improve surgical outcomes.

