#### 2.7.4. Primary Endpoint Analysis

The primary objective of this study is to evaluate the association between platelet function test results and clinical outcomes in patients undergoing elective and urgent CABG.

Summary Measures

Platelet function results will be summarized as mean ± standard deviation or median with interquartile range (IQR), depending on data distribution, for:AA channel (aspirin response)ADP channel (clopidogrel response)

Clinical outcomes, including MACCE, bleeding, re-exploration, and transfusion, will be reported as frequencies and proportions.

Method of Analysis

Correlation analysis: Pearson’s correlation for normally distributed data, Spearman’s rank correlation for non-parametric dataLogistic regressionEstimates the odds of postoperative events based on platelet resistance status (resistant vs. non-resistant)Adjusts for potential confounders (age, diabetes, renal function, surgical factors)Hierarchical data structure: Generalized estimating equations (GEE) or mixed-effects models will be used to account for repeated measures of platelet function over time.

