### 3.2. Platelet Function and Clinical Outcomes

Platelet function test results will be analyzed at three timepoints: preoperative baseline, postoperative discharge, and six-week follow-up. The degree of platelet inhibition will be reported as percentage inhibition in response to arachidonic acid and adenosine diphosphate pathways, reflecting aspirin and clopidogrel effectiveness, respectively.

The prevalence of aspirin and clopidogrel resistance in the study population will be determined based on predefined cutoff values from the TEG6s Platelet Mapping system. Differences in platelet responsiveness between groups will be evaluated using repeated measures analysis of variance or non-parametric alternatives, depending on data distribution.

The primary analysis will assess correlations between platelet function test results and major adverse cardiovascular and cerebrovascular events, including myocardial infarction, stroke, cardiovascular death, postoperative bleeding complications, and the need for surgical re-exploration. Univariate correlations will be explored using Pearson or Spearman correlation coefficients, while logistic regression models will estimate the odds ratios for adverse outcomes associated with platelet resistance.

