## 5. Potential Implications

By systematically assessing platelet function in the perioperative period, this study may provide critical insights into the prognostic relevance of antiplatelet resistance. Prior observational research suggests that pre- and postoperative platelet reactivity profiles may serve as early indicators of risk, enabling clinicians to identify patients at heightened risk for ischemic complications [5,11]. Additionally, studies have demonstrated that conventional aspirin doses (100 mg daily) may be insufficient in suppressing thromboxane synthesis in the early postoperative period due to accelerated platelet turnover [11,12]. The potential for transient resistance to resolve spontaneously, as reported in previous investigations, highlights the dynamic nature of platelet responsiveness and underscores the importance of individualized antiplatelet strategies [12].

Beyond individual risk stratification, the findings from this study may inform broader clinical practice by guiding the development of personalized antiplatelet regimens tailored to patients’ pharmacodynamic profiles. Previous studies, such as the BOCLA-Plan and tailored dual antiplatelet strategies using CYP2C19 genotyping, have demonstrated that dose adjustments or alternative antiplatelet agents can effectively overcome resistance [13,14]. If the present study validates the predictive utility of PFT, it could provide the foundation for future randomized trials evaluating personalized antiplatelet approaches, ultimately improving outcomes in CABG patients.

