## 7. Future Directions

Inter-individual variability in platelet responsiveness is influenced not only by clinical and perioperative factors but also by genetic determinants. Single nucleotide polymorphisms affecting platelet receptor pathways and antiplatelet drug metabolism—most notably variants in genes such as CYP2C19 involved in clopidogrel activation—have been shown to contribute to reduced antiplatelet efficacy and adverse cardiovascular outcomes. Integration of pharmacogenomic testing with platelet function assessment may therefore offer a more comprehensive approach to individualized antiplatelet therapy. Although genetic testing was beyond the scope of the present study due to its observational design and regulatory considerations, future studies incorporating combined platelet function and pharmacogenomic profiling may further refine risk stratification and therapeutic decision-making in CABG patients.

Should the study demonstrate a robust correlation between perioperative platelet function and postoperative outcomes, the findings may pave the way for future large-scale trials assessing the clinical utility of PFT-guided antiplatelet strategies. Specifically, randomized investigations evaluating tailored therapy based on individual platelet reactivity profiles could help bridge the existing gap between mechanistic understanding and therapeutic decision-making. Additionally, long-term follow-up studies examining the durability of platelet function trends beyond the immediate postoperative phase may further elucidate the trajectory of antiplatelet resistance and refine patient management strategies.

Taken together, this study is expected to contribute meaningful insights into the evolving field of CABG pharmacotherapy. By systematically analyzing platelet function patterns and correlating them with postoperative outcomes, this investigation holds the potential to advance precision medicine in surgical myocardial revascularisation, ultimately improving patient safety and optimizing antiplatelet management in CABG populations.

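### The planned correlations and odds ratios answer the association objective but not the risk-stratification and predictive-utility claims, because no planned measure quantifies discrimination

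*Protocol article*

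**What the plan says.** **Objective.** Section 1 sets the primary objective as determining the association between perioperative PFT results and clinical outcomes. Sections 2.6.1 and 2.7.4 repeat this.

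**Wider claims.**
- The Abstract states that "the study seeks to determine whether PFT can stratify risk and improve patient management".
- Section 2.1.2 presents the design as valid for evaluating postoperative risk stratification.
- Section 4 gives the purpose of relating reactivity to outcomes as "to determine whether PFT can serve as a reliable risk stratification tool for CABG patients".
- Section 5 continues: "If the present study validates the predictive utility of PFT, it could provide the foundation for future randomized trials".
- Section 7 names the result that might lead to large trials of PFT-guided strategies: "Should the study demonstrate a robust correlation between perioperative platelet function and postoperative outcomes".

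**Planned outcome analyses** (2.7.4 and 3.2).
- "Univariate correlations will be explored using Pearson or Spearman correlation coefficients".
- "logistic regression models will estimate the odds ratios for adverse outcomes associated with platelet resistance". Section 2.7.4 adjusts this model for age, diabetes, renal function and surgical factors.
- GEE or "mixed-effects models will be used to account for repeated measures of platelet function over time".

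**Tone of interpretation.** Section 2.7.9 calls the analyses exploratory, asks for caution with p-values and puts the weight on effect sizes and confidence intervals. The Abstract also calls the analysis exploratory.

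**The concern.** An association and a usable risk classifier are different things. An odds ratio says that risk differs between resistant and non-resistant patients. It does not say what share of events falls in the resistant group, what share of event-free patients is labelled resistant, or how well the continuous readings rank patients by risk. Correlation, logistic and mixed models all estimate association, so none of the results named in 2.7.4 or 3.2 bears directly on whether PFT is reliable for stratification or has predictive utility. Section 7 names a correlation, and no measure of test performance, as the result that could lead to PFT-guided trials. At stake is whether the final report can support the wording of the Abstract and sections 4, 5 and 7.

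**Working it through.** **Inputs.** From section 2.1.1: d = 0.5, two-sided alpha 0.05, power 80%, minimum 63 patients, 20% attrition, target N = 100. From section 1: aspirin resistance in up to 38% of patients, which is an upper figure and is used here as one case. The article gives no event rate, so 5% to 30% is assumed.

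**1. The plan's own figure.** For two means, n = 2(1.960 + 0.842)²/0.5² = 62.8, that is 63 per group or 126 in total. With attrition, 63/0.8 = 78.75, which matches the stated 80 or so. Using 63 as a study total is a separate matter, and this point does not depend on it.

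**2. The design effect as discrimination.** If d is the difference in a PFT reading between patients with and without an event, and the readings are normal with equal variance, then AUC = Φ(d/√2) = Φ(0.354) = 0.638.

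**3. The weakest significant result for the binary resistance label.** Take N = 100 with 38 resistant and 62 not. For each event count, find the smallest excess among the resistant with Fisher p < 0.05. For a binary marker, AUC = (sensitivity + specificity)/2.

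| Events | Resistant vs not | OR | p | Sens. | Spec. | AUC | PPV |
|---|---|---|---|---|---|---|---|
| 5 | 5/38 vs 0/62 | infinite | 0.007 | 1.00 | 0.65 | 0.83 | 0.13 |
| 10 | 7/38 vs 3/62 | 4.44 | 0.040 | 0.70 | 0.66 | 0.68 | 0.18 |
| 20 | 12/38 vs 8/62 | 3.12 | 0.038 | 0.60 | 0.68 | 0.64 | 0.32 |
| 30 | 16/38 vs 14/62 | 2.49 | 0.046 | 0.53 | 0.69 | 0.61 | 0.42 |

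Worked row, 10 events: sensitivity 7/10 = 0.70; specificity 59/90 = 0.656; AUC (0.70 + 0.656)/2 = 0.678; PPV 7/38 = 0.184; OR (7 × 59)/(31 × 3) = 4.44.

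**4. Sensitivity to the assumptions.** Over N = 80 or 100, prevalence 20-40% and event rates 10-30%, the AUC at the significance threshold runs from 0.61 to 0.76. At about 5 events the pattern changes: in the 38-resistant case significance needs all five among the resistant, so the apparent AUC is high but rests on five patients.

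**5. Precision if an AUC is reported.** Hanley-McNeil: SE² = [A(1−A) + (n₁−1)(Q₁−A²) + (n₀−1)(Q₂−A²)]/(n₁n₀), with Q₁ = A/(2−A) and Q₂ = 2A²/(1+A). For A = 0.65, 10 events and 90 non-events: Q₁ = 0.4815, Q₂ = 0.5121, SE = √[(0.2275 + 0.531 + 7.98)/900] = 0.099, 95% CI 0.46 to 0.84. With 20 events and 80 non-events: SE = 0.073, CI 0.51 to 0.79.

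**The case against.** **The stated objective is association.** This stands. Correlation and adjusted logistic regression are suitable for it, so a reader who inferred that the study cannot answer its own question would go too far. The mismatch is between the planned analysis and the wider wording in the Abstract and sections 2.1.2, 4, 5 and 7.

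**Nobody says a significant odds ratio validates the test.** This also stands. A reader might infer it from sections 5 and 7, but section 5 is conditional, section 2.7.9 urges caution, and the next step named is further trials, not clinical use. Still, an odds ratio with its interval does not measure discrimination, and the article names no other criterion for its predictive claims.

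**Covariates are already handled.** In part. The adjusted model in 2.7.4 tests whether resistance status carries information beyond age, diabetes and renal function. It does not show how much prediction improves.

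**An unseen analysis plan may hold these measures.** It may, and their absence from a condensed article is not the point. The point is that the article itself ties predictive conclusions to correlation.

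**The illustration is selective.** Fair as far as it goes: the event rates are assumed and 38% is a ceiling. A low PPV also largely reflects a low base rate; the 10-event table still shows 18.4% against 4.8%, a real risk gradient. The ranges above are therefore given in place of one figure.

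**An AUC would be too imprecise to help.** It would be wide, as step 5 shows. That argues for modest conclusions, and against making an optimism-corrected gain in c-statistic a requirement for every outcome.

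**Conclusion.** The point holds as a gap between claim and measure; it is not an error in the analysis of the stated objective. The planned results can establish association. They cannot by themselves support wording about reliable risk stratification or predictive utility. The gap could matter in practice: the effect the study is sized on corresponds to an AUC of about 0.64, and a just-significant resistance effect at N = 100 goes with AUC 0.61-0.68 and PPV 0.18-0.42. These figures assume 38% resistant and event rates of 10-30%, and the first also assumes normal readings with equal variance. At about five events the apparent AUC would be about 0.83, too fragile to rely on. The exploratory framing in the Abstract and section 2.7.9 softens the consequence, so this is a cheap and worthwhile improvement.

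**What to change.** In 2.7.4, add for MACCE and for bleeding:
- the c-statistic of continuous AA and ADP percentage inhibition, with 95% CI;
- sensitivity, specificity, PPV and NPV, with CIs, at the predefined TEG6s cutoff already referred to in 3.2;
- added value over the clinical covariates, with optimism correction, only if event numbers allow.

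State that any claim of risk stratification or predictive utility rests on these figures. If the team prefers not to add them, reword the Abstract and sections 4, 5 and 7 to claim association only, and align the phrase in 2.1.2.

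**Cost.** A few lines of analysis on data already being collected; the cutoff measures come from the same two-by-two tables as the unadjusted odds ratios. No extra patients or samples are needed. The downside is wide intervals (about 0.46 to 0.84 for a true AUC of 0.65 with 10 events in 100), which will make the conclusion less favourable. The rewording route needs no analysis.

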## 5. Potential Implications

By systematically assessing platelet function in the perioperative period, this study may provide critical insights into the prognostic relevance of antiplatelet resistance. Prior observational research suggests that pre- and postoperative platelet reactivity profiles may serve as early indicators of risk, enabling clinicians to identify patients at heightened risk for ischemic complications [5,11]. Additionally, studies have demonstrated that conventional aspirin doses (100 mg daily) may be insufficient in suppressing thromboxane synthesis in the early postoperative period due to accelerated platelet turnover [11,12]. The potential for transient resistance to resolve spontaneously, as reported in previous investigations, highlights the dynamic nature of platelet responsiveness and underscores the importance of individualized antiplatelet strategies [12].

Beyond individual risk stratification, the findings from this study may inform broader clinical practice by guiding the development of personalized antiplatelet regimens tailored to patients’ pharmacodynamic profiles. Previous studies, such as the BOCLA-Plan and tailored dual antiplatelet strategies using CYP2C19 genotyping, have demonstrated that dose adjustments or alternative antiplatelet agents can effectively overcome resistance [13,14]. If the present study validates the predictive utility of PFT, it could provide the foundation for future randomized trials evaluating personalized antiplatelet approaches, ultimately improving outcomes in CABG patients.

## 6. Study Limitations

As an observational study, this research does not involve direct therapeutic interventions by the study team. However, PFT results will be conveyed to the clinical team caring for the patient, who may modify treatment based on their clinical judgment. The study itself will generate valuable data regarding platelet function trends and potential predictors of poor outcomes, contributing to a better understanding of antiplatelet resistance without directly altering patient management within the study framework.

This study does not include immediate postoperative PFT upon arrival to the intensive care unit. While such measurements may offer mechanistic insights, discharge sampling was selected to balance clinical feasibility, patient safety, and assessment of stabilized platelet function following early recovery and antiplatelet therapy initiation.

Additionally, as with all studies incorporating PFT, variability in assay methodology and interpretation remains a challenge, given the lack of universal standardization across testing platforms [6]. Furthermore, the study is designed to evaluate platelet function within a defined perioperative timeframe, yet long-term outcomes beyond the study period may also be influenced by additional variables such as medication adherence, comorbid conditions, and secondary prevention strategies.

While venesection poses minimal risk, the additional blood sampling may introduce slight inconvenience for participants, although efforts have been made to integrate sample collection within routine clinical care.

## 7. Future Directions

Inter-individual variability in platelet responsiveness is influenced not only by clinical and perioperative factors but also by genetic determinants. Single nucleotide polymorphisms affecting platelet receptor pathways and antiplatelet drug metabolism—most notably variants in genes such as CYP2C19 involved in clopidogrel activation—have been shown to contribute to reduced antiplatelet efficacy and adverse cardiovascular outcomes. Integration of pharmacogenomic testing with platelet function assessment may therefore offer a more comprehensive approach to individualized antiplatelet therapy. Although genetic testing was beyond the scope of the present study due to its observational design and regulatory considerations, future studies incorporating combined platelet function and pharmacogenomic profiling may further refine risk stratification and therapeutic decision-making in CABG patients.

Should the study demonstrate a robust correlation between perioperative platelet function and postoperative outcomes, the findings may pave the way for future large-scale trials assessing the clinical utility of PFT-guided antiplatelet strategies. Specifically, randomized investigations evaluating tailored therapy based on individual platelet reactivity profiles could help bridge the existing gap between mechanistic understanding and therapeutic decision-making. Additionally, long-term follow-up studies examining the durability of platelet function trends beyond the immediate postoperative phase may further elucidate the trajectory of antiplatelet resistance and refine patient management strategies.

Taken together, this study is expected to contribute meaningful insights into the evolving field of CABG pharmacotherapy. By systematically analyzing platelet function patterns and correlating them with postoperative outcomes, this investigation holds the potential to advance precision medicine in surgical myocardial revascularisation, ultimately improving patient safety and optimizing antiplatelet management in CABG populations.

## Figures and Tables

**Figure 1 jcdd-13-00035-f001:**
[figure not shown]
Schematic study design.

